### Randomised treatment allocation, blinding and sample-size estimation

Informed consent will be obtained from each participant. Subjects eligible for participation will be randomly assigned to one of the following study groups by using the Internet based randomisation software RANDOULETTE® (Institute of Medical Information Sciences, Biometry and Epidemiology, University of Munich):

• press needle acupuncture: 25 subjects

• no treatment control: 25 subjects

• press plaster acupressure: 25 subjects

Stratification for age will be performed, and an equal distribution between treatment arms (ratio of 1:1:1) will be warranted.

In this trial we will use acupressure (group C) as an intervention to compare acupuncture (group A). Patients and examiners will be blinded for the patients’ assignment to treatment arms A and C. Therefore, we use press needles (0.2 mm × 1.5 mm; Seirin New Pyonex®, Seirin Corp., Shizuoka City, Japan) in group A and non-invasive Seirin press plasters in group C - a device that has successfully been validated for blinding in acupuncture trials [17]. Press plasters do not contain a needle but a blunt knob and are in all other aspects identical to the press needles. According to group allocation, press needles or press plasters will be administered by an independent acupuncturist at the same defined acupuncture points. Instructions regarding point stimulation for subjects and study staff will also be identical. Thereby, patients and examiners will be blinded as laid down in the trial of Myazaki and colleagues who showed that neither patients nor therapists nor examiners know if a sharp tip or a blunt knob is located below the plaster. In contrast to Myazaki, patients will be allowed to stimulate their press device, so that an additional acupressure effect may be elicited, thereby enhancing the overall effects.

### Participating trial physicians

Participating trial physicians are employees of the Multidisciplinary Pain Centre, Department of Anaesthesiology, University of Munich, Germany. Their average qualification is at least equal to a third year resident in the field of anaesthesiology and specialised pain medicine. They contribute to all medical duties.

The acupuncturists are physicians at the Multidisciplinary Pain Centre, Department of Anaesthesiology, University of Munich, Germany, who have passed more than 360 hours of curricular teaching in TCM and acupuncture and who routinely use acupuncture in daily clinical practice.

### Anaesthetic proceedings

All standardised medication will be permitted according to the perioperative anaesthetic guideline and to the standard perioperative pain guideline, Department of Anaesthesiology, University of Munich, both based on general recommendations and guidelines of the German Society for Anaesthesiology (DGAI). In particular:

opioids and propofol for intraoperative anaesthesia will be administered by Target Control Infusion (TCI) according to the standard protocol. TCI is a software based on pharmacokinetic models according to Schnider, used in the Fresenius-Kabi Orchestra® Base Primea syringe pumps (Fresenius Kabi Group, Bad Homburg, Germany). It requires age, gender, height and total body weight as input for programming. The software calculates the lean body mass for the patient and determines doses and infusion rates accordingly to achieve the necessary drug concentrations at the effect site (brain). The aspired effect-site concentrations are reported in Table 1.

**Table 1 T1:** Estimated effect-site concentrations

	**Propofol**	**Sufentanyl**
Induction of anaesthesia	4.0 to 9.0 μg/ml	0.2 to 0.4 ng/ml
Maintenance of anaesthesia	3.0 to 4.0 μg/ml	0.12 to 0.22 ng/ml

The effect-site concentrations are targeted during induction and maintenance of anaesthesia and form part of the standardised anaesthetic procedure during surgery.

To avoid postoperative pain all patients receive metamizol 2.5 g iv-infusions and to prevent PONV they receive dexamethasone 8 mg iv and for prevention of gastric stress ulcer they receive ranitidine 50 mg iv during surgery.

Postoperatively, subjects are treated for pain with metamizol (4 × 1.25 g/day) and the opioid piritramide (PCA; 2 mg each 10 minutes; maximum dosage 30 mg/4 hours). In case of nausea and vomiting or shivering, patients are treated according to the clinical standard.

Variations of this guideline based regimen are allowed if medically indicated. All concomitant therapies or medication are documented in the subjects’ clinical record file.

### Interventions

Patients in the acupuncture and the acupressure group will receive a standardised treatment with either 12 press needles (sharp tip) or 12 press plasters (blunt knob) at 7 acupuncture points (Du 26 and Ren 17 (on the middle body line), and bilateral LI 4, HE 7, LV 3, ST 36 and PC 6; see Figure 2). The needles have been provided by the SEIRIN Corporation, Shizuoka City, Japan. The point regimen is based on inquiring national experts. Application of the press needles or press plaster is performed and documented by a licensed medical acupuncturist 12 to 24 hours prior to surgery. Application time is supposed to be 72 to 96 hours. Modification will be allowed, in particular less points according to the patient’s reaction during treatment.The patient will be instructed to press the needles or plasters as often as they like, especially when they are suffering from anxiety, pain or nausea and vomiting. Patients are given an illustrated summary of the acupuncture points with the respective key symptoms, for memorization (see Figure 2). Stimulation of the press needles or press plasters has to be done at least three times a day, each time at a minimum of four different points, each for about 30 seconds. If the patient is not able to perform the daily manipulation by herself, the trial physicians are required to manipulate instead. During emergence, that is starting with the end of anaesthetic drug administration, the trial team or the anaesthetist is required to stimulate at acupuncture point Du 26.

**Figure 2 F2:**
[figure not shown]
**Acupuncture points hand out.** The figure illustrates the seven acupuncture points as being distributed to the patients. The listed symptoms indicate the key indications for the respective points. The chart is handed out to the patients in the acupuncture (ACU) and acupressure (APU) groups, the given indications are thought as reminder for the patients of the possible treatment effects to be expected when self-palpating the respective points. Du 26 has to be pressed by the attending anaesthetist during emergence.

Patients allocated to the control group will undergo the standard anaesthetic procedure only.

### Outcome measures

Main outcome measure:

Time from extubation to ‘ready for discharge’ from the PACU is defined as the latest time necessary to achieve the minimum score allowing for discharge score as assessed in three independent recovery scores. The used scores include the Aldrete score [18], the Post Anaesthetic Discharge Scoring System PADSS; [19] and the modified In-House score for outpatients of the Department of Anaesthesiology, University of Munich (for comparison see Table 2). All scores consist of five items regarding different postoperative physiologic states of the patient, which are graded from 0 to 2 (see Table 2). A summated score of 9 to 10 indicates that the patient is ready for discharge. The In-House score includes three additional ‘yes-no’ questions assessing orientation, input and output which have to be answered with ‘yes’, too. If all scores are fulfilled the patient is graded as ready for discharge.

**Table 2 T2:** Recovery scores in the post anaesthesia care unit

	**Sub-items (0 to 2 points)**	**Aldrete score**	**PADSS**	**In-House score**
Activity	4 extremities, 2 extremities, 0 extremities	YES		
Respiration	Deep breath, Dyspnoea, Apnoea	YES		
Circulation/Vital Signs	BP ± 20 mm/20% to baseline, BP ± 20 to 50 mm/20 to 40% to baseline, BP ± 50 mm/40% to baseline	YES	YES	YES
Consciousness	Awake, Arousal on calling, Not responding	YES		
Colour	Normal, Pale, Cyanotic	YES		
Activity, Mental Status	Oriented and steady gait, Oriented or steady gait, Neither		YES	
Pain, Nausea, Vomiting	Minimal, Moderate, Severe		YES	YES, Pain and PONV are both individually assessed
Surgical Bleeding	Minimal, Moderate, Severe		YES	YES
Intake and Output	Oral fluids and voided, Oral fluids or voided, Neither		YES	
Ability to arise	By itself, no nausea, With assistance only, Not possible, Nausea			YES
Orientation^a^	Person, Place, Time			‘yes-no’ question
Intake^a^				‘yes-no’ question
Output^a^				‘yes-no’ question
*Score considered for discharge from PACU*		** *≥ 9* **	** *≥ 9* **	** *≥ 9 and fulfill all ‘yes-no’ questions* **

YES indicates that the item forms part of the questionnaire. Each item consists of three sub-items which are rated with 0 to 2 points with 2 points reflecting the normal physiologic state. ^a^concerns three items of the In-House score which can only be answered as ‘yes’ or ‘no’. All scores have to be 9 or greater for patients being considered ‘ready for discharge’. In case of the In-House score, the three ‘yes-no’ questions have to be answered with ‘yes’. PADSS: Post Anaesthetic Discharge Scoring System.

**Secondary outcome measure:**In the pre- the intra- and the postoperative period (in PACU and at the ward) additional outcomes will be assessed (Figure 1).

• Preoperative period

○ Preoperative anxiety (State-Trait Anxiety Inventory: STAI [20])

▪ at baseline

▪ in the morning of the surgical day

▪ immediately before induction of anaesthesia

○ Vital signs (heart rate and blood pressure) at baseline

○ Pain intensity at rest at baseline

○ Laboratory parameters according to the surgical preoperative standard at baseline

• Intraoperative period

○ Intraoperative drug consumption (analgesics, sedatives)

○ TCI effect-site concentrations

○ Vital signs (heart rate and blood pressure)

○ Bispectral Index (BIS) monitoring (recording starts prior to induction of anaesthesia)

○ Organisational time points (for example, incision to closure time; intubation to extubation time, and so on)

○ During emergence, the time point when stopping the TCI device, time to recovery of spontaneous breathing and time to extubation, time to eye opening, time to squeezing of the anaesthesiologists hand on command and orientation to time and place will be recorded if possible

○ About 15 minutes before the end of surgery, analgesia applied through the TCI pumps will be reduced (expected emergence 15 minutes) to facilitate recovery and time will be recorded. Time to extubation is defined as the time between end of anaesthesia and extubation.

• PACU

○ Time course and comparison of recovery scores (Aldrete score, PADSS, In-House scoring system)

○ Pain intensity

○ Analgesic consumption

○ Concurrent medication

○ Occurrence of surgical- or anaesthesia-related events

▪ PONV

▪ Shivering

▪ Others

○ Vital signs

• Postoperative period (on the ward)

• Patients will be visited after discharge from the PACU based on a fix scheme, which is six hours after, and three times daily on the two following postoperative days unless the patient has been previously discharged from the hospital. The following parameters will be assessed:

○ Vital signs

○ Pain intensity

○ Quantity and frequency of stimulated acupuncture points

○ Analgesic consumption

○ Concurrent medication

○ Occurrence of surgical- or anaesthesia-related events

▪ PONV

▪ Shivering

▪ Others

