### Data analysis

The aim of the statistical analysis is the comparison of the main outcome measure (period from extubation to ‘ready for discharge’ from PACU) between the three study groups (intervention groups acupuncture and acupressure and no treatment control). For this variable, an non-normal distribution is assumed. Hence, a nonparametric method, the Kruskal-Wallis test will be applied. *Post hoc* tests will be performed by pairwise comparisons of the three study groups by the Mann-Whitney *U*-test and subsequent Bonferroni adjustment for multiple comparison (*P*-value times three). Primary outcome is defined as the time to discharge from PACU in the press needle acupuncture group in comparison to the no treatment group.

For the secondary target variables, a method according to the distribution of data will be performed. For metric variables, the structure of a normal distribution will be tested by the Kolmogorov-Smirnov test. In case of a normal distribution, a one-way ANOVA will be calculated. Otherwise a nonparametric test for independent observations like the Kruskal-Wallis test will be carried out.

The analysis of categorical data is conducted by the chi-square goodness-of-fit test. The binary case is treated by the chi-square-test of independence.

Data analysis will be performed with the SPSS statistical software system, version 15.0 (SPSS Inc., Chicago, IL, USA) and with SAS/STAT® Software (SAS Institute Inc., Cary, NC, USA). All data entry will be carried out twice.

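### PACU analgesic totals and PONV and shivering counts cover a stay whose length the primary outcome governs, so a faster-recovering arm can look better on them with no analgesic or antiemetic effect

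*Protocol article*

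**What the plan says.** All references are to the protocol article.

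- **Primary outcome.** Under Outcome measures: "Time from extubation to ‘ready for discharge’ from the PACU is defined as the latest time necessary to achieve the minimum score" on three recovery scores. On the discharge rule: "If all scores are fulfilled the patient is graded as ready for discharge". Data analysis words the endpoint as departure itself: "Primary outcome is defined as the time to discharge from PACU".
- **Content of the scores.** Table 2 has an item for pain, nausea and vomiting in the PADSS. For the In-House score the same row reads "YES, Pain and PONV are both individually assessed". The In-House score also needs a yes on intake and on output.
- **PACU secondary outcomes.** The list includes pain intensity, "Analgesic consumption", and the occurrence of PONV and shivering. The text gives no time limit other than the PACU stay.
- **Ward secondary outcomes.** The same items are assessed at visits: "Patients will be visited after discharge from the PACU based on a fix scheme, which is six hours after". After that, visits are three times daily on the two following postoperative days, unless the patient has left hospital.
- **Analysis.** Data analysis names ANOVA or Kruskal-Wallis for metric secondary variables and chi-square tests for categorical ones. It states no allowance for length of observation.
- **Figure 1**, which marks assessment time points, is not reproduced in the text available.

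**The concern.** A cumulative dose or an event count depends on how long the patient is observed. Here the observation period in the PACU closes at an event that the primary outcome governs. If acupuncture shortens the stay and does nothing else, its patients have less time to request analgesic doses, vomit or shiver while in the PACU. The comparison would then show a benefit that only repeats the primary result.

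The link also runs the other way. Pain and PONV are scored in two of the discharge instruments, so the symptoms help set the length of the window in which they are counted. Stay can also be prolonged for reasons unrelated to pain, such as the intake and output questions, while patient-controlled doses continue to add up.

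This matters because the Discussion presents postoperative pain and side effects such as PONV and shivering as findings that the trial will deliver. A positive primary result could bring apparent analgesic and antiemetic benefits with it.

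**Working it through.** **1. The plan's own figure.** Table 3: one-way ANOVA, 3 groups, f = 0.4, α = 0.05, power 0.8. With N = 66, λ = N × f² = 66 × 0.16 = 10.56, the critical F is 3.1428 and power is 0.818. N = 63 gives 0.798. The stated 66 is reproduced, and this point does not change it.

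**2. Illustration of the PACU opioid total.** From the plan: 25 patients per arm and patient-controlled doses in 2 mg steps. Assumed, because the documents give no figures: mean PACU time 120 min in the slower arm, coefficient of variation 0.4, and mean use of 3 mg/h varying between patients. Hourly use has the same distribution in both arms, so there is no analgesic effect. Only length of stay differs. The test is a two-sided Mann-Whitney at 0.05 between two arms, with 3,000 runs (simulation error near 5% is √(0.05 × 0.95/3000) = 0.4 percentage points).

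| Stay in faster arm | Mean PACU dose, slower vs faster arm | False positives, PACU total | False positives, fixed 24 h total |
|---|---|---|---|
| 120 min (equal) | 6.0 vs 6.0 mg | 4.4% | 4.5% |
| 108 min (10% shorter) | 6.0 vs 5.4 mg | 7.0% | 5.3% |
| 96 min (20% shorter) | 6.0 vs 4.8 mg | 11.2% | 4.7% |
| 84 min (30% shorter) | 6.0 vs 4.2 mg | 23.2% | 3.7% |
| 60 min (50% shorter) | 6.0 vs 3.0 mg | 65% | 5.1% |

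**3. Where the plan's effect size falls.** The assumed SD is 0.4 × 120 = 48 min. Sample size calculation labels 0.4 as d in the text and as f in Table 3.
- Read as d, the difference is 0.4 × 48 = 19 min, or 16% of 120.
- Read as f with three groups, the extreme arms lie between 0.4 × 3/√2 = 0.85 SD and 0.4 × √6 = 0.98 SD apart. That is 41 to 47 min, or 34 to 39%.

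On these assumptions, an effect of the size planned for is not at the harmless end of the table.

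**4. PACU PONV.** With an assumed constant rate of 0.15 per hour, the expected proportion is 1 − exp(−0.15 × hours).
- 120 min: 25.9%
- 96 min: 21.3%
- 84 min: 18.9%

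In 25 patients these are 6.5, 5.3 and 4.7 expected cases, a difference of about one to two patients.

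**5. First ward visit.** With a 120 min stay it falls 6 + 2 = 8.0 h after extubation. A 24 min shorter stay makes it 7.6 h, a 5% shift. If pain halves every 6 to 24 h (assumed), recorded pain rises by a factor 2^(0.4/6) = 1.047 to 2^(0.4/24) = 1.012. For a 60 min shift the factors are 1.122 to 1.029.

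**6. Later ward visits.** These follow the postoperative day, not PACU discharge, so they do not shift.

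**The case against.** A reader might infer that all PACU and ward pain, analgesic and PONV outcomes are distorted, that any effect on recovery time is enough, and that the secondary objectives cannot be interpreted. The documents do not support this.

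- Up to six of the seven ward visits follow the calendar. Preoperative anxiety and the intraoperative outcomes precede the PACU altogether.
- The first ward visit is anchored to PACU discharge, but the bias there is a few per cent for plausible differences in stay.
- Figure 1 may set pain-rating times within the PACU. Ratings at set times would be little affected. Set rating times would not, however, equalise total doses or event occurrence over unequal stays.
- Readiness is not departure. Patients may leave after the criteria are met, which weakens the link. Data analysis treats the two as the same, so the link is not removed.
- The text does not say that consumption will be analysed as a raw PACU total, and details of derivation may stand in a fuller document. What is printed, though, lists the outcomes by location, and nothing in it corrects for length of stay.
- A dose rate that is constant over the stay is doubtful when pain and PONV themselves gate discharge. The sizes above are illustrative. With a stay 10% shorter, the inflation is slight.
- These are secondary outcomes in a pilot that itself says confirmatory studies would be needed.

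These arguments narrow the point to cumulative PACU analgesic use and PACU occurrence of PONV and shivering. For those outcomes they do not answer it.

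**Conclusion.** The point holds for cumulative PACU analgesic consumption and for PACU occurrence of PONV and shivering. Their observation period ends at an event governed by the primary outcome, so a faster-recovering arm can show lower totals and fewer events with no true analgesic or antiemetic effect. The bias is small for a 10% shorter stay and grows with the difference. The illustrative false-positive rate for the opioid total is about 11% at 20% shorter and 23% at 30% shorter, against 4 to 5% for a fixed 24-hour total. These figures rest on an assumed mean stay, spread, dose rate and constancy of that rate, none of which the documents give. For PONV the expected difference is only one to two patients per arm. The primary analysis and the sample size are untouched. The shift at the first ward visit is too small to justify changing the visit schedule.

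**What to change.** Before analysis, define the between-arm comparisons of analgesic use, PONV and shivering over fixed intervals from extubation, for example 0 to 2 h and 0 to 24 h, across PACU and ward. Extubation is already the zero point of the primary outcome, and both locations already record these items. Report the PACU totals as descriptive only.

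Keep the visit schedule. Fifty of the 75 patients had been included when the article was submitted, so re-timing the first ward visit would create two schedules in one small trial for little gain. Instead, record the actual time from extubation to the first ward visit, so that it can be reported by arm or adjusted for in a sensitivity analysis.

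The cost is some extra data handling, with no added patients or visits. The main limit is the records. Anaesthetic proceedings says that all concomitant medication is documented, but not that each dose is timed. PONV or shivering between PACU departure and the first ward visit can be placed in an early window only if its time was noted. Check this for the patients already enrolled before fixing the shortest window, and state how patients who leave hospital before 24 h are handled.

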### Sample size calculation

No sample size calculation could be established because at the time of designing the trial there were no parameters available from prior studies. However, we estimated the sample size on the basis of an *a priori* analysis using G*Power (Version 3.1.3, University of Düsseldorf, Germany, see Table 3). We conservatively anticipated the effect size of the tested intervention to be small to medium (d = 0.4, according to Jacob Cohen [21]), which results in a sample size of 66 patients for three study groups. A further adjustment for non-parametric testing and drop outs by 15% results in a total sample size of 75 patients.

**Table 3 T3:** Sample size calculation

F tests:	ANOVA: Fixed effects, omnibus, one-way		
Analysis:	*A priori*: Compute required sample size		
Input:	Effect size f		= 0.4
	α err probability		= 0.05
	Power (1-β err probability)		= 0.8
	Number of groups		= 3
Output:	Noncentrality parameter λ		= 10.5600000
	Critical F		= 3.1428085
	Numerator df		= 2
	Denominator df		= 63
	Total sample size		= 66
	Actual power		= 0.8

A priori analysis as calculated and exported by G*Power (Version 3.1.3, University of Düsseldorf, Germany), anticipating a small to medium effect size f = 0.4, the α-error = 0.05 and the power = 0.8.

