## Discussion

The AcuARP trial investigates the effectiveness of acupuncture on post anaesthetic recovery and its use as an adjunct therapy to improve patient’s recovery in the whole perioperative setting.

Inclusion and exclusion criteria were held pragmatic in order to facilitate screening and recruitment. The chosen trial population is homogeneous and the operations undertaken are common; hence a maximised and improved routine care would be of general interest.

Limitations include the restricted sample size as the trial was planned as a pilot study. In case of a positive study outcome, further confirmatory studies will be needed. In addition, a standardised clinical procurement, using strictly standardised anaesthesia and standardised acupuncture regimen may impede generalizability of the findings.

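### The sample-size paragraph treats Cohen's d and f as one quantity: 66 patients follow from f = 0.4, not from the stated d = 0.4

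*Protocol article*

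**What the plan says.** The Sample size calculation section first says that no prior parameters were available for a calculation, and then gives an a priori power analysis. Its basis is worded as "We conservatively anticipated the effect size of the tested intervention to be small to medium (d = 0.4", and the sentence goes on: "which results in a sample size of 66 patients for three study groups". An increase described as 15%, for non-parametric testing and drop-outs, brings the total to 75.

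Table 3 reports the software run. The procedure is "ANOVA: Fixed effects, omnibus, one-way" and the effect-size input is f = 0.4, with alpha 0.05, power 0.8 and three groups. The footnote repeats the verbal label for the other measure: "anticipating a small to medium effect size f = 0.4, the α-error = 0.05 and the power = 0.8". No conversion from d to f is given.

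The Data analysis section plans a Kruskal-Wallis test with Bonferroni-adjusted pairwise Mann-Whitney tests, and names press needle acupuncture versus no treatment as the primary comparison.

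**The concern.** Cohen's d is the difference between two means in units of the within-group SD. Cohen's f, the input to the ANOVA procedure, is the SD of the group means divided by the within-group SD. The same number on the two scales describes effects of very different size. Here 0.4 appears as d in the text and as f in Table 3, with the same description attached to both.

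What is at stake is the meaning of the printed 80%. A reader of the paragraph will take it that 75 patients give good power for a modest effect, chosen cautiously. If the modest effect is what was meant, the power is far lower. If the entered value is what was meant, the effect is not modest. In both cases a non-significant result could be given more weight against a modest benefit than the design supports.

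**Working it through.** **Inputs.** From Table 3: three groups, alpha 0.05, f = 0.4, N = 66. From the text of the same section: d = 0.4, final N = 75. From the randomisation section: "an equal distribution between treatment arms (ratio of 1:1:1) will be warranted", so 22 per arm at N = 66 and 25 per arm at N = 75. From Data analysis: the primary contrast and a Bonferroni factor of three.

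**Step 1: reproduce Table 3.** For a one-way omnibus F test, lambda = N × f², with 2 and N − 3 degrees of freedom.
- f = 0.4, N = 66: lambda = 66 × 0.16 = 10.56, critical F = 3.1428, power = 0.818.
- f = 0.4, N = 63: power = 0.798, so 66 is the smallest multiple of three that reaches 0.80.

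Table 3 is internally correct, for f = 0.4.

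**Step 2: convert d = 0.4 to f.** Take 0.4 SD as the largest difference among three equal arms.
- Third arm midway: f = d/√6 = 0.4/2.449 = 0.163.
- Third arm equal to one of the others: f = d√2/3 = 0.4 × 0.471 = 0.189.

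These are the smallest and largest f that a range of 0.4 SD allows in three equal groups.

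**Step 3: omnibus F power at those values.**

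| f | Power, N = 66 | Power, N = 75 | N for 80% power |
|---|---|---|---|
| 0.163 | 0.195 | 0.218 | 366 |
| 0.189 | 0.248 | 0.279 | 276 |
| 0.20 (two-group shortcut d/2) | 0.275 | 0.310 | 246 |
| 0.40 (as entered) | 0.818 | – | 66 |

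The last column is before any inflation. The N = 75 column assumes that every patient is evaluable and that nothing is lost to rank testing.

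**Step 4: what f = 0.4 means as a difference.**
- Third arm midway: 0.4 × √6 = 0.98 SD.
- Third arm equal to another: 0.4 × 3/√2 = 0.85 SD.

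Relative to the stated effect, that is 0.85/0.4 = 2.1 to 0.98/0.4 = 2.4 times.

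**Step 5: the primary contrast at d = 0.4.** Two-sided two-sample t test, noncentrality d√(n/2).

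| n per arm | Noncentrality | Power, alpha 0.05 | Power, alpha 0.05/3 |
|---|---|---|---|
| 22 | 0.4 × √11 = 1.33 | 0.254 | 0.133 |
| 25 | 0.4 × √12.5 = 1.41 | 0.283 | 0.154 |

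This contrast does not depend on where the acupressure arm lies.

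**The case against.** The strongest defence is that d is a slip for f. Table 3 and its footnote both say f, and only the sentence in the text says d. On that reading 66 patients and 80% power are correct. This stands as far as it goes, and it is why the low power figures cannot be presented as settled. It does not save the paragraph: f = 0.4 needs extreme arms 0.85 to 0.98 SD apart, so *conservatively* and *small to medium* do not describe the number used.

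A second objection is that the power range rests on assumptions. The text speaks only of the tested intervention, not of the largest of three differences, and the planned test is Kruskal-Wallis, not ANOVA. Both remarks are fair. The 20–28% should be labelled as omnibus F power with 0.4 SD as the largest difference. Even the more favourable d/2 shortcut gives only 28–31%, and the primary contrast taken alone gives no more than 28%.

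A third is that the article discloses its limits. It calls the trial a pilot, says no calculation could be established from prior data, and lists the restricted sample size as a limitation in the Discussion. This lessens the consequence, but a power of 0.8 is still printed and used to reach 66 and then 75.

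A reader might infer more: that the step to a confirmatory trial depends on statistical significance and will usually be missed. The Discussion says "In case of a positive study outcome, further confirmatory studies will be needed". That is a caution that a positive pilot needs confirmation. It sets no significance threshold for proceeding and does not say what follows a null result. Nor do the documents show that the trial must be enlarged to 276 or 366 patients; those figures only measure the gap.

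**Conclusion.** Wrong as written, on either reading.

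- **If d = 0.4 is the intended largest between-arm difference:** 66 does not follow from it. Omnibus F power is about 20–25% at N = 66 and 22–28% at N = 75, not 80%. For acupuncture versus no treatment, t-test power is about 25–28% unadjusted and 13–15% after the Bonferroni factor.
- **If d is a slip for f:** the 80% holds for f = 0.4, but the effect assumed is 0.85 to 0.98 SD between the extreme arms, and the two descriptions of it are wrong.

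The figures assume equal arms, a common SD and normal-theory tests. They approximate the planned rank tests, whose power depends on a distribution that the article does not give. The conclusion rests on the d-to-f arithmetic alone, not on any outside label for the size of f. It concerns the justification and the reading of a null result; it does not invalidate the design or the planned analysis.

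**What to change.** Keep the sample size and correct the paragraph and the Table 3 footnote:

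1. Name one effect measure and use it in both places, with the d-to-f conversion if both are mentioned.
2. State that 66 evaluable patients give about 80% omnibus power only for f = 0.4, that is, extreme arms 0.85 to 0.98 SD apart.
3. State that omnibus F power for a largest difference of d = 0.4 is about 20–28% over 66 to 75 patients.
4. Delete *conservatively* from the text, and *small to medium* from the text and the footnote.
5. State that a non-significant result in this pilot does not rule out an effect of d = 0.4.

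The cost is a few sentences and a less favourable power statement. No patients are added, and neither conduct nor analysis changes, so the correction remains possible with the 50 patients reported as included under Trial status.
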